# Influence of a periodized circuit training protocol on intermuscular adipose tissue of patients with knee osteoarthritis: protocol for a randomized controlled trial

**DOI:** 10.1186/s12891-018-2325-y

**Published:** 2018-11-30

**Keywords:** Intermuscular fat, Circuit workouts, Adipokines, Quadriceps, Inflammation, CT scan, Physical therapy, Rehabilitation

## Abstract

**Background:**

The objective of this study is to analyze the influence of a 14-week periodized circuit training protocol on patients with knee osteoarthritis (OA), in randomized intervention groups, on thigh intermuscular adipose tissue (interMAT), body composition, systemic inflammation, cartilage degradation, and its repercussion on pain, functional performance and quality of life.

**Methods:**

This study presents a protocol for a randomized controlled trial. Sixty selected participants diagnosed with knee OA grades II and III, 40–65 years old and BMI < 30 kg/m^2,^ will be randomly divided into three groups:periodized circuit training, strength training, and educational protocol. The circuit training and strength training protocols consist of 14-week training protocols conducted 3 times a week. The circuit training group will perform selected exercises previously stratified as light, moderate, and intense, arranged progressively in a circuit model, the strength group will perform regular strength exercises, and the educational protocol group will participate in a 14-week protocol with lectures twice a month about healthy lifestyles. Baseline and follow-up evaluations will be conducted for thigh interMAT (computed tomography), body composition (DXA), inflammation (IL-1β, IL-6, IL-10, TNF-α, leptin, and adiponectin), and joint degradation biomarkers (uCTX-II and sCOMP), performance-based tests (30s Chair Stand Test, 40 m Fast-paced Walk Test and Stair Climb Test), quadriceps and hamstring maximal isometric voluntary contraction (MIVC), and questionnaires (WOMAC and pain catastrophizing scale). Repeated measures ANOVA will be used to compare differences between groups (circuit training X strength training X educational protocol) at the different times of assessment (baseline x follow-up or baseline x during protocol x follow-up) for each of the dependent variables. When significant main effects were found, the pots hoc Bonferroni test will be used to identify statistical differences. A significance level of 5% (*p* < 0.05) will be adopted.

**Discussion:**

This will be the first randomized controlled trial to assess the effects of a circuit training protocol on patients with knee OA on thigh intermuscular adipose tissue (interMAT). Given the prevalence and impact of OA and the widespread availability of this intervention, assessing the efficacy of a low-cost, non-pharmacological, and non-invasive treatment for knee OA patients has the potential for immediate and high clinical impact.

**Trial registration:**

ClinicalTrials.gov, NCT02761590, registered in May 4, 2016.

**Electronic supplementary material:**

The online version of this article (10.1186/s12891-018-2325-y) contains supplementary material, which is available to authorized users.

## Background

Knee osteoarthritis (OA) is a chronic inflammatory degenerative joint disease that commonly causes pain and limits activity, placing a significant burden on healthcare services [1–3]. Changes in body composition such as a decrease in muscle mass associated with an increase in adipose tissue are characteristics that can contribute to OA progression. Moreover, fat infiltration can change the orientation of muscle fibers, thereby reducing the power production capacity [4, 5].

Higher amounts of intermuscular adipose tissue (interMAT) in the thighs of patients with knee OA has been considered clinically significant due to the negative associations with knee extensor strength, physical function, and the systemic inflammatory process [6–8]. InterMAT can be considered a deposit of ectopic fat similar to visceral adipose tissue, which can release proinflammatory cytokines [9].

Modulation of the inflammation present in OA has been related to the occurrence of some cytokines, especially interleukin-1β (IL-1β), interleukin-6 (IL-6), and tumor necrosis factor-α (TNF-α), which are critical mediators of metabolic disturbance and increased catabolism of joint tissues [10], and may lead to progressive loss of muscle mass [11] and interfere with cartilage degradation [12]. Adipocytes release adipokines such as leptin and adiponectin, which can cause and exacerbate chronic low-level systemic inflammation. Studies suggest that leptin may act to regulate chondrocyte metabolism and has been related to the metabolic (non-mechanical load) effect of obesity on joint disease and could explain the association between joint disease and metabolic syndrome disorders [10, 13, 14]. Adiponectin has also been proposed as a systemic biomarker of OA. Plasma adiponectin was significantly higher in a population of OA patients [11]. In muscle, adiponectin has been shown to increase fatty acid oxidation and glucose uptake, and to attenuate local inflammation [15].

The catabolic processes of articular cartilage evaluation present in OA are very important for better understanding of its pathogenesis, as well as being a method to evaluate its development in the short term. Biomarkers, such as uCTX-II and COMP, have the capacity to detect early joint degradation in degenerative diseases such as OA [16], being, therefore, significantly associated with the incidence and progression of OA [17].

Although a number of biochemical markers of joint tissue turnover have been developed and tested, the majority of studies have been limited to cross-sectional studies of people with and without OA or observational studies of OA progression [18]. It has been described in the literature that physical exercise modifies the inflammatory condition of the body, especially by modifying the circulation of IL-6 [19] and increasing anti-inflammatory cytokines such as IL-10 [20]. Thus, these cytokines are related to basic morbidities under the influence of different types of exercises.

Considering the reduction in physical activity and quality of life found in individuals with knee OA (due to the influence of inflammation and changes in body composition) [21], non-pharmacological, conservative clinical guidelines are encouraged, and physical exercises are recommended due to their beneficial effects, low potential for adverse effects, and low cost [22–24].

Studies assessing the effects of exercise on knee OA are widespread and are intended to reduce pain, and improve muscle strength, stability of joints, and aerobic fitness, leading to improvement in functionality [24, 25]. Although several studies have demonstrated its effectiveness in increasing strength, reducing pain, and improving functionality [26], there is no evidence of the effect of exercise on thigh composition (adipose tissue and muscle mass) and the related impairment in individuals with knee OA.

It is known that physical exercise can increase muscle mass and muscle strength [27] and has shown promise in protecting the knee joint and reducing inflammatory cytokines [28, 29]. In a systematic review, Juhl et al. (2014) investigated training protocols used to treat patients with knee OA and reported that optimal exercise programs for this population should focus on improving aerobic capacity, quadriceps strength, and lower limb performance [25]. However, Bennell and Hinman (2011) reported that a combination of both resistive and aerobic training is better suited to deal with the various complications associated with OA [23]. Similarly, Nguyen et al. (2016), in a review study related to the efficacy and safety of exercise therapy and strength training, reported that although rehabilitation is a key treatment in OA and widely recommended, the ideal method for therapy programs remains inconsistent [30]. In this way, enriching the reasons for exercise prescription seems to be a gap that needs filling.

One way to combine the benefits of these modalities is circuit training, used to stimulate both systems, which promotes cardiovascular and muscle strengthening [31, 32]. The effects of circuit training on several chronic disorders are known and positive effects have been shown on body composition by reducing body fat, which can be achieved by a repeated series of exercises, with little or no rest interval between them [33]. This type of exercise can more effectively activate lipolysis of adipose tissue than conventional aerobic training [31, 34]. This allows many people to participate in the same training session due to low total duration of the exercises [31, 33, 35, 36], which promotes high retention and adherence of participants [37].

Despite having recently attracted the interest of researchers due to the potential benefits that this technique provides, the effects of a periodized circuit training protocol on interMAT remain unclear. Only three studies in the consulted literature have evaluated the effects of circuit training on knee OA patients. These studies showed a reduction in body mass and adipose tissue (assessed by dual X-Ray absorptiometer (DXA)), increase in muscle strength, improved knee function, and a reduction in pain compared with a control condition [38–40]. However, the training protocol did not follow a periodized model.

Adipose tissue concentration and muscle quality are directly linked with physical activity level and exercise intensity. Few studies have explored the physical activity level of their sample [41–43] and used it to normalize or discuss data. In older adults, a greater physical activity level is associated with less visceral adipose tissue, subcutaneous fat, and interMAT [44].

To date, no studies have assessed the changes in muscle fatty infiltration in the thigh after exercise and its implications, such as inflammation levels in the knee OA population. There is evidence that exercise in combination with diet is effective for decreasing total body fat mass, inflammation levels, and pain, in addition to improving physical function in overweight and obese adults with knee OA [45]. In overweight and obese adults, resistance training improved body composition, including reduction in thigh interMAT [46]. Meanwhile, in older fallers, there were no significant changes in thigh interMAT content after 3 months of resistance training [47]. It seems that exercise can decrease fat infiltration in thigh muscles of overweight and obese. However, in older fallers this was not seen.

Considering the possible alterations in muscle function and morphology caused by the presence of fat tissue in thigh muscles, it is essential that new study proposals involving a periodized circuit training protocols identify not only body fat reduction, but also the local effects of the amount of interMAT.

It is understood that a randomized controlled trial, the gold standard in intervention studies [48], is the best way to evaluate new treatments for a given variable, as suggested by Messier et al. (2015) in the study recommendations, design, and conduct of clinical trials in patients with OA [49]. The present study protocol has an investigative character and we emphasize its originality, mainly because the influence of periodized circuit training on the main study variable (interMAT) is still unknown.

The results of this research may contribute to elaboration of future treatment strategies and early intervention in the causative and potentiating factors of the disease, verifying the effects of a low-cost, non-pharmacological, and non-invasive treatment to provide subsidies for better rehabilitation planning for patients with knee OA.

## Methods/Design

### Aim

The main objective of the present study will be to compare the influence of 14-weeks of periodized circuit training with strength training and an educational protocol on thigh interMAT and body composition. Secondarily, the present study will investigate these effects on indicators of cartilage degradation and systemic inflammation, and its repercussions on physical function, pain, and quality of life in patients with knee OA.

Our general hypothesis is that both circuit training and strength training protocols will promote decreases in thigh interMAT, associated with improvement in body composition and muscle strength, and a reduction in inflammatory cytokine concentration (IL1β, IL6, TNF-α), pain, and stiffness in patients with knee OA, leading to consequent improvement in quality of life, compared to the educational protocol. However, it is hypothesized that these benefits, mainly related to the improvement in the body composition and reduction in interMAT will be more evident after the circuit training, compared to the strength training. Additionally, it is also hypothesized that biomarkers of joint degradation may signal exercise efficiency for both groups over the application of both training protocols.

The following methodology is in full agreement with the SPIRIT (Standard Protocol Items for Randomized Trials) recommendations [50–52] [50–52] and the Osteoarthritis Research Society International (OARSI) recommendations for RCTs [53] to ensure methodological rigor. Consolidated Standards of Reporting Trials (CONSORT) [54] guidelines will be followed for reporting the results in a subsequent article.

### Study design

The present proposal is characterized as a single-blinded randomized controlled trial design. This is the first version of the study protocol, submitted to the registry of clinical trials *Clinical Trials* (clinicaltrials.gov) and registered in May 4, 2016, under identification code NCT02761590.

### Ethical aspects

This study was approved by the Research in Human Ethics Committee (CEP) of the Federal University of São Carlos-SP. Participants will be informed about the procedures that will be performed throughout the research, and after agreeing to participate, will sign an informed consent form (ICF). This study will be conducted according to Resolution 466/12 norms of the National Health Council on research involving humans.

### Blinding

The outcome assessor will be blind to group allocation and will not be involved in the interventions or attend any of the testing. The physical therapists supervising the exercise intervention sessions will not be blinded. The statistician will be blinded to group allocation prior to completion of the statistical analysis. With training and standard operating procedures, it is anticipated that any performance bias due to lack of blinding will be minimized.

### Recruitment

Participants from the community of São Carlos, Brazil, will be invited to participate in this study. Three main methods will be used to recruit potential participants: advertisements will be placed in local newspapers, magazines, and social media. Potential participants will be invited to complete a phone interview to pre-screen their eligibility to ensure that they meet the study selection criteria prior to randomization. If deemed eligible, an appointment will be scheduled to confirm eligibility, sign the ICF, and complete baseline evaluations.

### Sample

To determine the sample size, the data of thigh interMAT from the study of Griessmann et al. (2014) were considered [55]. 16 participants per group was stipulated through a two-tailed hypothesis test, with a 5% level of significance and 80% test power.

Considering the possible sample loss in the course of the study, 20 subjects each, totaling 60 participants of either sex will be included in this study.

To be eligible, participants will be required to fulfill the following criteria:i.Aged between 40 and 65 years;ii.KOA clinically diagnosed fulfilling the American College of Rheumatology classification criteria of knee pain on most days of the past month and radiographically, classified as grades 2 or 3 according to Kellgren and Lawrence criteria [56].iii.Knee pain for ≥3 months;iv.Overall average knee pain in the last week ≥4 on a 0 to 10 Visual Analogue Scale (VAS).

The exclusion criteria are:i.Knee surgery;ii.Body mass index (BMI) ≥30 kg/m^2^;iii.Previous history of lower limb trauma;iv.Physical therapy, chiropractic, or acupuncture treatment or exercises specifically for the knee within the previous 6 months;v.Walking more than 30 min continuously daily or participating in a regular (more than twice a week) exercise program;vi.Current or past (within 3 months) oral or intra-articular corticosteroid use;vii.Systemic arthritic conditions such as rheumatoid arthritis;viii.Inability to walk unaided as this is necessary for some of the physical testing;ix.Medical condition precluding safe exercise such as uncontrolled hypertension, heart condition, cardiac pacemaker use, chronic diseases, impaired renal function, or any other medical condition that precludes participation in the study [57, 58];x.History of severe muscular lesions (above grade I);xi.Motor impairment due to neuromuscular diseases;xii.Cognitive deficits that compromise understanding of the tests;xiii.Starting any other exercise protocol or physical therapy during the study.xiv.Unable to comply with the protocol such as inability to attend therapy session or attend assessment appointment at the University.xv.Kellgren and Lawrence grades 0, 1, and 4.

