**Fig. 1 Fig1:**
[figure not shown]
Timeline of study procedure; EM: Educational meeting sessions; DXA: dual X-Ray absorptiometry; MVIC: maximal voluntary isometric contraction

On day 1, participants will be guided and familiarized with the experimental procedures to be performed. An evaluation form (personal and anthropometric data, blood pressure, knee pain, and previous medical history) and the informed consent form will be completed. During the same visit, the body composition test (Dual Energy X-ray Absorptiometry - DXA) will be performed and the participant will receive a referral for the knee radiographic exams.

Day 2 will be scheduled after the OA radiographic diagnosis and classification. During this visit, the WOMAC *(Western Ontario and McMaster Universities)* and Pain Catastrophizing Scale (PCS) questionnaires will be completed. Subsequently, the participants will perform three functional performance-based tests (40 m fast-paced walk test, 30 s chair stand test, and stair climb test), and the strength test*.* The functional performance tests and the strength test will be performed in random order. Participants will then receive the referral and guidelines for the computed tomography exam for thigh composition (adipose tissue and muscle mass) analysis and blood and urine samples will be collected for inflammatory and collagen activity marker analysis, identifying the systemic responses to exercise. After the baseline evaluations (Days 1 and 2), participants will be randomized through a randomization website (https://www.random.org/) into three groups: periodized circuit training, strength training, and educational protocol. The group distribution will be balanced for: number of males and females, age, body mass index (BMI), and radiographic severity. A researcher not involved with the evaluations and intervention sessions will be in charge of conducting the participant randomization and balance distribution. During and at the end of the 14 weeks intervention protocols, follow-up evaluations will be scheduled (Fig. 1).

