### Statistical analysis

Data analysis will be performed using the software *Statistical Package for the Social Sciences* version 20.0 (*SPSS* Inc., Chicago, IL, USA). An intention to treat analysis will be conducted for all data analyses. Initially, descriptive analysis of variables will be performed as mean, standard deviation, and coefficient of variation. Next, normality and homogeneity of variance will be checked by the Kolmogorov-Smirnov test and Levene’s test, respectively**.** If normal distribution of data is not observed, the same transformations will be carried out, to allow the application of parametric tests**.**

Two-way ANOVA (group X time) will be conducted for the dependent variables. When significant differences were observed in the group or interaction, will be performed a post-hoc Bonferroni Test. For all measured variables, the estimated sphericity will be examined in accordance with Mauchly’s W Test, and the Greenhouse-Geisser correction will be used as needed. For comparison between moments, for uCTX-II, sCOMP, and MVIC repeated measures ANOVA (baseline X during protocols X follow-up) will be performed. When significant main effects are found, the Bonferroni test will be used to identify statistical differences. For IL1-β, IL-6, TNF-α, leptin, adiponectin, WOMAC, PCS, DXA, computed tomography, and functional performance-based tests, the t-test will be used (baseline X follow-up). For all analyzes a significance level of 5% will be adopted (*p* < 0.05). No interim efficacy or subgroup analyses are planned.

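### The 80% power at 16 per group is stated for an unadjusted two-tailed 5% test; for the Bonferroni-corrected pairwise comparisons that the plan uses, the same effect has about 64-65%

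*Protocol article*

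**What the plan says.** The Sample section bases the size on thigh interMAT data from a cited study and states: "16 participants per group was stipulated through a two-tailed hypothesis test, with a 5% level of significance and 80% test power". Recruitment is then raised to allow for losses: "20 subjects each, totaling 60 participants of either sex will be included in this study". The article does not give the test that was sized, the contrast, the difference or the SD.

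Participants are randomised "into three groups: periodized circuit training, strength training, and educational protocol". The Aim section hypothesises that both exercise programmes reduce interMAT relative to education. It adds that the benefits, mainly those in body composition and interMAT, "will be more evident after the circuit training, compared to the strength training". Together these involve all three pairs of arms.

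In the Statistical analysis section, "Two-way ANOVA (group X time) will be conducted for the dependent variables", and then: "When significant differences were observed in the group or interaction, will be performed a post-hoc Bonferroni Test". The Abstract also plans a Bonferroni post-hoc test. The overall significance level is 5%. The primary outcome, named in the Thigh computed tomography section, is interMAT.

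**The concern.** The power statement and the analysis use different thresholds. The size was set with a "two-tailed hypothesis test, with a 5% level of significance", but a pairwise group difference will be declared only if it passes the Bonferroni threshold for three comparisons. A test with 80% power at 5% has less at 1.67%, and the enrolment of 20 per arm covers dropout, not this correction.

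The omnibus group-by-time test cannot say which arm is better, so the corrected pairwise step is the only planned between-group test that addresses the directional hypotheses. A reader who relies on the printed 80% would give too much weight to a non-significant pair. This matters most for circuit versus strength, where two active programmes are compared and both are expected to reduce interMAT.

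**Working it through.** **Inputs from the article.** n = 16 per group, two-sided alpha 0.05, power 80%, 20 enrolled per group (Sample); three arms (Procedures); Bonferroni post-hoc tests (Statistical analysis). Three arms give three pairs, so alpha per pair is 0.05/3 = 0.0167.

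**Assumption.** The sized test compared two groups, on the scale that will be analysed.

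**Step 1: the plan's own figure.** Without an effect and SD, 16 cannot be derived forward, so it is inverted for the standardised difference d.
- Normal approximation: d = (1.960 + 0.842) × √(2/16) = 0.991.
- Noncentral t, 30 df (two groups): d = 1.024.
- Noncentral t, 45 df (error pooled over three groups): d = 1.012.

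The loss allowance reproduces with 20% attrition: 16/(1 − 0.20) = 20.

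**Step 2: change only alpha.** The noncentrality is d√(n/2), and d is fixed by the stated 80%, so the unreported effect size is not needed. By the normal approximation at n = 16, power = Φ(1.960 + 0.842 − 2.394) = Φ(0.408) = 65.8%.

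| Completers per arm | Normal | t, two-group df | t, pooled df |
|---|---|---|---|
| 16 | 65.8% | 64.2% | 64.7% |
| 20 | 77.0% | 76.4% | 76.6% |

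In each column d is solved and power evaluated with the same type of degrees of freedom.

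**Step 3: size for 80% per corrected pair.** Normal: 2 × (2.394 + 0.842)² / 0.991² = 21.3, so 22. Both t calculations also give 22.

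**Step 4: does the ANOVA gate matter?** Simulating a significant omnibus F test first, then the Bonferroni pair, gives about 64-66% at n = 16, depending on which d is used and where the third mean lies. The gate hardly changes the result.

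**Step 5: if a three-group F test was sized.** 80% power at 16 per group implies f = 0.463. The largest pairwise difference is then d = 0.983 if one group differs from two equal ones, and 1.135 if the means are equally spaced. Corrected power for that pair is 62% and 76%.

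**Step 6: a smaller difference (illustration).** At half the design difference (d about 0.51), power per corrected pair is about 16% with 16 per arm and 20% with 20. The half is an assumption; the article gives no expected circuit-versus-strength difference.

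**Step 7: the closed alternative.** Omnibus test at 5%, then unadjusted pairwise tests at 5% only if it is significant. By simulation, power for a pair at the design difference is about 68-76% at n = 16 and 80-86% at n = 20. The lower end has the third mean midway; the upper end has it equal to one of the pair. With d solved at the pooled df, which matches the pooled-error test, the n = 16 range is 68-75%. Simulated family-wise error under the global null was about 5%.

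**The case against.** The strongest objection is that the premise is not printed. The Sample section names no test, effect or SD, and an article may leave these to the full protocol. That stands: 64-65% is conditional, and 16 itself can be neither confirmed nor refuted. But the issue is a conflict between two printed statements, the unadjusted power and the Bonferroni step, not the missing detail. The F-test reading also leaves the largest pair below 80%.

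A second objection concerns scale. The group-by-time analysis with two time points tests change. If the sizing used a between-person SD, the SD of change is that SD × √(2(1 − r)), where r is the baseline-to-follow-up correlation. Corrected power at 16 per arm would then be about 47-48% at r = 0.3, 64-65% at r = 0.5, 75-76% at r = 0.6 and 88% at r = 0.7. This stands too: a high enough correlation would bring the corrected power above 80%. The article claims no such gain, and a low correlation would make matters worse.

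Third, the Statistical analysis section also assigns a baseline-versus-follow-up t-test to computed tomography, and the sizing might have been for that. A within-group test cannot answer a between-group aim, so it does not rescue the 80%.

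Fourth, the article nowhere claims 80% for each corrected pair. That is so, but it states no other power, and the pairwise step carries the hypotheses.

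A reader might also infer that circuit versus strength is the leading hypothesis, or that the trial is shown to have only 16-20% power for it. The documents do not support either. The Aim section puts both exercise arms versus education first, and the half-effect is illustrative. Nor is Bonferroni itself at fault; it controls the error rate properly.

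**Conclusion.** The concern holds in conditional form. The stated 80% applies to an unadjusted two-tailed 5% test and does not carry over to the corrected pairwise comparisons. If a two-group contrast was sized on the analysed scale, power per pair is about 64-65% at 16 completers (66% by normal approximation) and 76-77% with no losses, against 22 per arm needed for 80%. The shortfall of about 15 percentage points at 16 does not depend on the unreported difference and SD, because the stated 80% fixes their ratio. It does depend on the sized and analysed tests sharing a scale. If a three-group F test was sized, the range is about 62-76% for the largest pair.

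This does not show that 16 was miscalculated from the cited data, or that more participants must be enrolled. It shows that the power statement does not describe the planned analysis. Power for circuit versus strength is lower still if that difference is smaller than the design effect.

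**What to change.** 1. Restate the power for the corrected pairwise comparison. Name the sized test and contrast, the interMAT difference, the SD and its scale (follow-up value or change). If a two-group test on the analysed scale was sized, the figures are about 64-65% at 16 completers per arm and 76-77% at 20. This costs one or two sentences and no participants.

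2. State that circuit versus strength will be reported as an estimated difference with a confidence interval, and that a non-significant result is not evidence of no difference. This costs one sentence.

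3. Optionally, replace the Bonferroni step for the primary outcome with the closed procedure, which is valid for exactly three groups: a between-group omnibus test of change in interMAT at 5%, then unadjusted pairwise tests at 5% only if it is significant. Power rises to about 68-75% at 16 and 80-86% at 20. The gain is partial at 16, and reaching 80% needs essentially no losses. The small cost is that unadjusted pairwise intervals are not simultaneous, which should be stated. If this option is taken, the restated power in item 1 should be that of the closed procedure.

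### The 80% power for 16 per group is stated at an unadjusted 5% level, while the between-arm pairs are tested with Bonferroni: on a two-group, same-scale reading, pairwise power is about 65% with 16 completers per arm and about 77% with 20

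*Protocol article*

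**What the plan says.** All references are to the protocol article.

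- **Sample.** "16 participants per group was stipulated through a two-tailed hypothesis test, with a 5% level of significance and 80% test power". The section points to interMAT data from a published study but prints no difference, SD or type of test, and mentions no adjustment for several comparisons. It continues: "Considering the possible sample loss in the course of the study, 20 subjects each, totaling 60 participants of either sex will be included".
- **Aim.** The main objective is to "compare the influence of 14-weeks of periodized circuit training with strength training and an educational protocol on thigh interMAT" (and on body composition). The hypotheses are that both training arms do better than education and that circuit training does better than strength training. Thigh computed tomography names interMAT as the primary outcome.
- **Procedures.** Participants are randomized "into three groups: periodized circuit training, strength training, and educational protocol".
- **Statistical analysis.** A two-way group by time ANOVA is followed by pairwise tests: "When significant differences were observed in the group or interaction, will be performed a post-hoc Bonferroni Test". The same section also lists a baseline versus follow-up t-test for computed tomography and sets 5% for all analyses.

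**The concern.** The hypotheses are about pairs of arms. An omnibus group by time result shows that the arms differ somewhere, but not which arm is better. That is left to the post-hoc step, and with three arms a Bonferroni step tests each of three pairs at 0.05/3. The power in the Sample section is quoted at 0.05, three times that level.

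What is at stake is how a null result is read. If the trial finds no difference between circuit and strength training, readers will take it as coming from a trial with an 80% chance of detecting the planned difference. On the plainest reading, with 16 completers per arm, the chance of missing that difference is about 35% rather than 20%. If all 20 complete, it is about 23%.

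**Working it through.** **Inputs**

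- From Sample: n = 16 per group after losses, 20 enrolled, two-sided alpha 0.05, power 0.80.
- From Procedures: three arms, so 3 × 2 / 2 = 3 pairs.
- From Statistical analysis: Bonferroni post-hoc test. Inferred level per pair: 0.05/3 = 0.0167.
- Not given: difference, SD, type of test, baseline/follow-up correlation r. The 16 cannot be reproduced from raw inputs, but n, alpha and power together fix the standardised difference d for any assumed test.

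**Step 1. Recover the plan's own figure (two-group reading)**

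Normal approximation: d = (1.960 + 0.842) × √(2/16) = 2.802 × 0.3536 = 0.99. Putting this back returns n = 16 and power 0.800.

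Noncentral t with 30 df: d = 1.024.

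**Step 2. Same d at 0.05/3**

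Noncentrality is d × √(n/2): 1.024 × √8 = 2.895 for n = 16, and 1.024 × √10 = 3.237 for n = 20. Power is the probability that the noncentral t exceeds the two-sided 0.0167 critical value in absolute size.

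| Completers per arm | Error df | Critical t | Power at d = 1.024 | d needed for 80% |
|---|---|---|---|---|
| 16 | 30 (two arms) | 2.536 | 64.2% | 1.20 |
| 16 | 45 (three arms pooled) | 2.487 | 65.9% | 1.18 |
| 20 | 38 (two arms) | 2.505 | 76.4% | 1.06 |
| 20 | 57 (three arms pooled) | 2.467 | 77.7% | 1.05 |

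The normal approximation (d = 0.99, critical value 2.394) gives 65.8% and 77.0%.

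Simulating the planned sequence, a 5% omnibus test followed by Bonferroni, gives about 65-66% with 16 and 77-78% with 20 for the pair at d = 1.02. The omnibus step hardly changes the result.

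**Step 3. Does the result depend on which SD was used?**

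Step 2 takes the sizing SD to be on the scale of the analysis. With two time points, group by time compares changes. If the SD was instead between-person at one time, the SD of change is SD × √(2(1 − r)), and the effective difference is 1.024 / √(2(1 − r)). Power at 0.05/3 with 16 per arm (30 df / 45 df):

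| r (assumed) | Power |
|---|---|
| 0.5 | 64% / 66% |
| 0.6 | 75% / 77% |
| 0.65 | 82% / 83% |
| 0.7 | 88% / 89% |
| 0.8 | 97% / 98% |

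The break-even is r = 1 − (1.024/d80)²/2, where d80 is the last column of the first table. Using the two-arm df, r = 0.64 with 16 completers and 0.54 with 20. Using the pooled df, it is about 0.62 and 0.52.

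**Step 4. Other tests that may have been sized**

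- Three-arm omnibus F test: 16 per group and 80% imply Cohen's f = 0.463. If one arm differs from the other two, the largest pair is d = 0.98, with power 62% (n = 16) or 74% (n = 20). If the means are equally spaced, the extreme pair is d = 1.14, with power 76% or 87%, and an adjacent pair has 20% or 26%.
- Paired test within one arm: the implied standardised change is 0.75. If the comparator does not change, corrected between-arm power is 35-37% (n = 16) or 45-47% (n = 20).

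**The case against.** The strongest reply is that the Sample section never claims 80% for the post-hoc pairs. Both the omnibus test and the baseline versus follow-up t-test named for computed tomography run at 5%, so the figure may be right for the test it was computed for. The effect, SD and test type are not printed, a condensed article may leave them to the full protocol, and the divisor 3 is inferred. The design also enrols 20 per arm and specifies intention to treat, so 64-66% alone would show only the less favourable case.

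Much of this stands. A reader might infer that pairwise power must fall below 80% however the 16 was obtained. The document does not support that. Sizing on a between-person SD, with a baseline/follow-up correlation above about 0.64 (16 completers) or 0.54 (20 completers), gives 80% or more for the corrected pairs. An omnibus sizing with equally spaced means also gives about 87% for the extreme pair with 20 completers. The absence of the effect size is not itself the point.

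Two parts do not stand. The baseline versus follow-up t-test does not compare arms, and the omnibus test does not say which arm is better, so neither carries the hypotheses in the Aim. The phrase "two-tailed hypothesis test" also fits a two-group comparison better than an F test. And since the step from 16 to 20 is explained by expected loss, 16 is the plan's own completer number; both figures should be shown.

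**Conclusion.** The point holds in a limited form. The power is stated at an unadjusted 5% level, while the between-arm comparisons that answer the main objective are Bonferroni-corrected, and nothing in the article connects the two.

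If the sizing test compared two groups on the same scale as the analysis, the 80% becomes about 64-66% with 16 completers per arm, a loss of 14 to 16 points. With 20 completers it is about 76-78%, a loss of 2 to 4 points. The 80% then applies to a difference of about 1.2 SD (16) or 1.05 SD (20), not 1.02 SD.

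This rests on three assumptions: three pairs in the correction, a two-group sizing test, and a sizing SD on the analysis scale. If the third fails and the correlation is high enough, there is no shortfall. If the omnibus test was sized, 80% is right for that test but not in general for the pairs.

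**What to change.** Keep the recruitment target of 60. In the Sample section:

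1. Name the comparison to which the 80% refers, and say whether the SD behind it is cross-sectional or of change.
2. Restate the power for a pairwise between-arm comparison of interMAT change at the Bonferroni level actually used, for both 16 and 20 completers per arm. If the two-group, same-scale reading is the one used, these are about 65% and 77%, with 80% reached at about 1.2 SD and 1.05 SD. If another test or SD was used, give the corresponding figures instead of these.

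The cost is a short change of wording, with no extra participants or procedures. The downside is that the stated power may become less favourable.
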